In this second version of the protocol, we added two safety outcomes. The first is patient adherence to anticoagulation prescribed at hospital discharge. The second outcome is incidence of the main complication (stroke/pulmonary embolism) at a median follow up. This amendment is felt necessary due to relatively frequent patient-reported non-adherence to anticoagulants observed during telephone interviews.

Data for adherence rate to anticoagulants will be obtained from an additional review of the audio recording of the interview. This will be performed by one of the two reviewers.

Incidence of complications at median follow up will be assessed via a second telephone contact with recruited participants (patients or caregiver), using the same contact information provided at the time of recruitment. We will make a maximum of five attempts of contact, after which participants will be considered lost at follow up.

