## **Statistical methods**

A full data management plan and a full statistical analysis plan (SAP) has been revised and approved by the scientific board prior to study start. The SAP does not include details of data on rate of adverse events and decision rules for arm(s) or study termination, as this is not appropriate to this study. After SAP signature by the scientific board (i.e. prior to any statistical analysis), the study database will be locked. Any changes to the protocol-specified or SAP-specified planned analyses that are made after the database lock will be described in the clinical study report.

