### Telephone Interview

- 1. Could you tell me the name of the medical condition you have been diagnosed with and explain what it is in your own words?**

☐ Insufficient ☐ Sufficient ☐ Good ☐ Excellent

- 2. Have you been prescribed new take-home medications in the Emergency Department for this medical condition?**

☐ Insufficient ☐ Sufficient ☐ Good ☐ Excellent

- 3a). (For those patients who have been prescribed new take-home medications) What are these drugs for and for how long should you take them? What are the possible complications of your medical condition?**

☐ Insufficient ☐ Sufficient ☐ Good ☐ Excellent

- 3b). (For patients who have not been prescribed new take-home medications) Do you know why you have not been prescribed new medications? When are you going to have a follow-up visit? What are the possible complications of your medical condition?**

☐ Insufficient ☐ Sufficient ☐ Good ☐ Excellent

- 4. What symptoms would worry you enough to return to the Emergency Department?**

☐ Insufficient ☐ Sufficient ☐ Good ☐ Excellent

- 5. While in the Emergency Department did you get a chance to ask your doctor questions on your medical condition?**

☐ No, none of them ☐ Only a few of them ☐ Nearly all I had in mind ☐ Yes, all of them

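### The two added safety outcomes are not soundly measured as written: adherence is read from recordings that never ask about it, and stroke/PE incidence has no fixed window and telephone-only ascertainment

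*Protocol*

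**What the plan says.** The Outcomes section of the protocol adds two safety outcomes in its second version.

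- **Adherence.** "The first is patient adherence to anticoagulation prescribed at hospital discharge". The source is existing audio: "Data for adherence rate to anticoagulants will be obtained from an additional review of the audio recording of the interview". There is a single rater: "This will be performed by one of the two reviewers". The comprehension and satisfaction scores, by contrast, have two independent raters and a written interpretation scheme.
- **Complications.** "The second outcome is incidence of the main complication (stroke/pulmonary embolism) at a median follow up". The source is a second telephone contact with the recruited participant (patient or caregiver) at the number given at recruitment. For those not reached: "We will make a maximum of five attempts of contact, after which participants will be considered lost at follow up".

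The reason given is: "This amendment is felt necessary due to relatively frequent patient-reported non-adherence to anticoagulants observed during telephone interviews".

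The Statistical methods section states: "The SAP does not include details of data on rate of adverse events". The same sentence also excludes decision rules for stopping, and calls both unsuited to this study. The section says the SAP was approved before the study started, whereas the two outcomes were added after interviews had begun.

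**The concern.** An outcome can be no better than the question that elicits it. The adherence outcome was added because non-adherence seemed frequent, but it is to be taken from an interview designed to test knowledge. A patient can name every drug, dose, purpose and duration, earn full marks, and never have taken a dose. Because the calls fall within 48 hours, even a clear remark speaks only to starting the drug.

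For stroke/PE, a median follow-up time is a summary computed once follow-up is over. It cannot be scheduled, so the incidence has no time base. The only stated source is a telephone call, and the events being counted are ones that can stop a person answering.

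At stake is false reassurance, or an uninterpretable percentage, from two outcomes labelled as safety.

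**Working it through.** **1. The plan's own figures.** The protocol gives no rate, precision or sample size for either safety outcome. Its only design figure concerns the primary score, and it reproduces. With a difference of 20% × 10 = 2 points and SD 4, the normal formula 2(1.96 + 0.84)²(4/2)² gives 63 per arm and the t-test version 63.8, so 64; 64/0.90 = 71.1, so 72 per arm and 144 in total. The point here does not depend on this figure, except that the planned 10% loss is 0.10 × 144 = 14.4 patients.

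**2. Does the interview elicit drug-taking?** From the Telephone Interview and Interpretation of patients' answers supplements:

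| Question | Subject | Asks about actual use? |
|---|---|---|
| 1 | Name and explanation of the diagnosis | No |
| 2 | Whether new drugs were prescribed; scored on recall of names and dosage | No |
| 3a | "What are these drugs for and for how long should you take them"; also complications | No: intended, not actual |
| 3b | Patients given no new drugs | Not applicable |
| 4 | Symptoms that would prompt a return | No |
| 5, 6 | Chance to ask questions; clarity | No |

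The scoring scheme contains no adherence item.

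**3. What unprompted remarks can establish.** Let s be the share of recordings that mention drug-taking and a the share adherent among those. With the rest unknown, the true rate lies between s·a and s·a + (1 − s). The documents give neither value; taking a = 0.9 as an assumption:

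| s (assumed) | Lower bound | Upper bound | Width |
|---|---|---|---|
| 0.3 | 27% | 97% | 70 points |
| 0.5 | 45% | 95% | 50 points |
| 0.8 | 72% | 92% | 20 points |

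**4. Risk window.** An incidence is events divided by patients at risk over a stated interval. No interval from discharge, and no date for the second call, appears anywhere in the protocol.

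**5. Loss that depends on the event.** Let p be the true incidence, l₁ the loss among patients with an event and l₀ the loss among the others. Then observed incidence = p(1 − l₁) / [p(1 − l₁) + (1 − p)(1 − l₀)]. I take l₀ = 10%, the planned loss; p and l₁ are assumptions.

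| p | Expected events in 144 | Observed, l₁ = 50% | Observed, l₁ = 75% |
|---|---|---|---|
| 1% | 1.4 | 0.6% | 0.3% |
| 3% | 4.3 | 1.7% | 0.9% |
| 5% | 7.2 | 2.8% | 1.4% |

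Worked line: 0.03 × 0.5 = 0.015; 0.97 × 0.9 = 0.873; 0.015/0.888 = 1.7%. If loss is unrelated to the event (l₁ = l₀), the observed incidence equals p.

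**6. Scale.** The planned loss of about 14 patients exceeds the expected number of events in every row. The secondary analyses in the supplement show 69 and 68 of 72 reached at the first call, so 3 and 4 lost (4.2% and 5.6%); loss at the second call is not reported. For precision, zero events in 72 gives an exact upper 97.5% limit of 1 − 0.025^(1/72) = 5.0%.

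**The case against.** The strongest reply is that the recordings do contain adherence information. The amendment exists because non-adherence was heard in these calls, and the Ethics and dissemination section has interviewers refer on patients who do not know of, or decline, the anticoagulant. This stands: a reader might infer that adherence cannot be measured at all, and the protocol does not support that. What remains is that use is not systematically elicited. Remarks heard in some calls show that the problem exists, not how common it is. The referral step also means that stroke/PE is counted after interviewers have acted on some of these patients.

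Second, the follow-up call may be answered by a caregiver, so it is wrong to say that severely affected patients cannot be captured. But the Eligibility criteria enrol a caregiver only where the patient lacked capacity or could not safely receive the instructions at discharge. A patient enrolled in their own right has no stated proxy.

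Third, several harsher inferences lack support. No text says that a silent recording counts as adherent or that a lost patient counts as event-free; the zero-score rule in the Analysis strategy concerns scores. No common calendar date is set for the second call, so greater exposure for early recruits is a guess, and randomisation should roughly balance follow-up between arms in any case. The 5.0% is a confidence limit, not an event rate, so it cannot show that losses exceed the event rate. The adverse-event sentence is a wording conflict with the added outcomes, not evidence that they fail.

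Finally, coding rules, denominators and intervals may sit in an SAP that is not shown, and their absence is not counted here. What is asked, when, and from which source are data-collection choices that no analysis can recover afterwards.

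**Conclusion.** The point holds in limited form. Adherence as written rests on unprompted remarks made within 48 hours of discharge, as heard by one rater. It can support a statement that some patients had not started treatment, but not an adherence rate. Stroke/PE incidence has no defined risk window, and telephone-only ascertainment leaves it open to loss related to the event itself.

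The size cannot be derived from the documents. The adherence bands (20 to 70 points wide) and the understated incidences (3% read as 0.9% to 1.7%) rest on assumed shares of informative recordings and assumed differential loss. They show what could happen, not what did.

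Severity is moderate. Both outcomes were added late and have no stated power, and the comprehension score, its sample size and its analysis are untouched.

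**What to change.** - **Adherence.** At the second call already planned, ask every patient prescribed an anticoagulant (or the caregiver) one scripted question: was it started, and is it still being taken? Use these patients as the denominator.
- **Recordings.** Report the recording-based measure separately, as volunteered early non-initiation, with *not mentioned* treated as missing. Do not pool it with the prompted answers.
- **Stroke/PE.** Count stroke/PE and death within one fixed window from discharge, the same for all patients, with event dates. Make the second call after that window closes.
- **Patients not reached.** Check the two hospitals' own records, and keep those still unresolved as unknown.
- **Reporting.** Present both outcomes descriptively with exact 95% confidence intervals.
- **Text.** Reconcile the adverse-event sentence in Statistical methods with the outcomes added in Outcomes.

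The cost is one extra question, a records check for the few patients not reached, and amendment wording. Two limits remain: the prompted adherence measure is taken later than 48 hours and so answers a different question from the recordings, and the two hospitals' records will miss events treated elsewhere.

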## **Participants timeline**

Patient enrolment will take place in the emergency departments without any time restriction, including night shifts and festivities. Nevertheless, it is possible that the enrolment of eligible patients does not occur in a continuous fashion, as not all the doctors serving in the department participate in the study.

Prior to the discharge of eligible patients, the SIs will invite patients (or caregivers) to participate to the study, explaining its purpose and the methods used. Patients (or caregivers) willing to participate will sign the consent, provide a valid telephone number and are assigned to the study or control group. After patient's discharge, the SIs will transmit the telephone number to the PIs in charge of conducting interviews.

Telephone interviews will be carried out within 48 hours from discharge, using an institutional telephone station located in the emergency department of the IRCCS Fondazione Policlinico San Matteo Hospital.

The telephone station is connected to the institutional computer situated in the same room, which is provided with a free downloadable software for phone call management. All recordings will be stored on the same computer and each file is named with a progressive number code.

The equipment used to carry out phone interviews are situated in the same room where all files related to the study will be stored (consents, discharge letters, opaque envelopes for randomization).

Interviewers will try to contact patients (or caregivers) telephonically with a maximum of five attempts, after which the patients will be considered lost to follow-up.

During a patient's permanence within the emergency department, the SIs do not anticipate to the patient the content of the telephone interview, in order not to influence their answers.

## **Sample size**

We hypothesize a median score for the primary outcome to be 10 points in the control group, whereas we expect a 20% higher score in the intervention group as suggested by current literature, with standard deviation 4 and non-normal distribution. Group sample sizes of 64 and 64 achieve 80% power to detect this difference with alpha error 5% using a two-sided Mann-Whitney test assuming that the actual distribution is uniform. (Note: this number represents the total number of patients with either DVT or AF, within each study group, since we do not expect differences in the effect by diagnosis).

Since we expect the number of patients lost to follow-up to be 10%, we plan to enroll 72 patients in each group (144 patients in total).

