## ***Analysis strategy***

The main analysis will be performed with an ITT perspective, considering patients lost to follow-up as having score zero.

A secondary analysis will be performed “on treatment”, i.e. on patients who have been reached at the follow-up call.

A sensitivity analysis will also be performed, considering patients lost to follow-up as “average” knowledge (inputting the missing score with mean score across both groups).

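### The stated 80% power belongs to patients with an observed score; the main analysis, which scores lost patients zero, has about 62% at the planned 10% loss

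*Protocol*

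**What the plan says.** Protocol, Sample size, sets the planning values. The control score is given as "We hypothesize a median score for the primary outcome to be 10 points in the control group"; for the effect, "we expect a 20% higher score in the intervention group"; and the spread comes "with standard deviation 4 and non-normal distribution". The test is a "two-sided Mann-Whitney test assuming that the actual distribution is uniform". From these the section concludes "Group sample sizes of 64 and 64 achieve 80% power to detect this difference with alpha error 5% using a two-sided Mann-Whitney test". It continues: "Since we expect the number of patients lost to follow-up to be 10%, we plan to enroll 72 patients in each group".

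Protocol, Analysis strategy, defines three analyses. The main one follows an intention-to-treat perspective, "considering patients lost to follow-up as having score zero". Patients actually reached by telephone form a secondary analysis. A sensitivity analysis gives lost patients the overall mean score.

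Protocol, Statistical analyses, lets the Shapiro–Wilk test decide between a parametric and a nonparametric comparison. Protocol, Outcomes, puts the primary score on a 0–18 scale, so zero is its floor.

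**The concern.** The step from 64 to 72 replaces patients who are expected to have no score. It protects power only in an analysis that leaves those patients out. The main analysis does not leave them out: it gives each the worst possible score. All 72 per group are then analysed, but about one in ten carries an extreme low value that is the same in both arms and says nothing about the video.

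This pulls the arms together and widens the spread. The 80% is therefore attached to an analysis that the protocol calls secondary, while the power of the main analysis is not given anywhere in the section. A reader who takes the 80% at face value will overrate the trial's planned ability to detect the targeted effect.

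**Working it through.** **Inputs.** From Sample size: 10 v 12 points (20% of 10 = 2), SD 4, uniform distribution, two-sided 5%, 64 per group, 10% loss, 72 enrolled per group. From Analysis strategy: lost patients score 0. Assumed here, because the protocol does not say: loss is equal in both arms and unrelated to the score.

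**1. The protocol's own figures.** Standardised difference 2/4 = 0.5. A two-sample t test needs 63.8, so 64 per group, and has 80.1% power at 64. The asymptotic efficiency of Mann-Whitney relative to the t test is 1 for uniform data, so 64 carries over. Then 64/0.9 = 71.1, rounded up to 72. Both figures reproduce.

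**2. Mann-Whitney at 64, directly.** A uniform distribution with SD 4 has width 4√12 = 13.86. Hence P(video > control) = 1 − (1 − 2/13.86)²/2 = 0.634. Noether's formula gives a total of 7.849/(3 × 0.1339²) = 146, or 73 per group, for 80%. At 64 per group, power = Φ(√(3 × 128) × 0.1339 − 1.96) = Φ(0.66) = 75%. Simulation of the test gives 75–76% at 64 per group and reaches 80% at about 71–72.

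**3. The main analysis: 72 per group, 10% zeros.**
- Difference in means: 0.9 × 2 = 1.8.
- Control variance: 0.9 × (16 + 100) − 9² = 23.4 (SD 4.84). Video variance: 0.9 × (16 + 144) − 10.8² = 27.36 (SD 5.23). Pooled SD: √25.38 = 5.04.
- t test: 1.8/5.04 = 0.357, power 56.7%.
- Mann-Whitney: the assumed control scores start at 10 − 6.93 = 3.07, so every zero lies below every observed score. The probability of a higher video score, ties counted half, becomes 0.81 × 0.634 + 0.09 + 0.005 = 0.6085. Noether's formula gives Φ(√(3 × 144) × 0.1085 − 1.96) = Φ(0.295) = 62%. Simulation also gives 62%.

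**4. Which test applies.** In trials simulated as in step 3, Shapiro–Wilk rejected normality in at least one arm more than 99% of the time. The protocol's rule therefore leads to Mann-Whitney, and 62% is the relevant figure.

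**5. Variants, 72 per group.**

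| Setting | Mann-Whitney | t test |
|---|---|---|
| 10% chance of zero, uniform scores | 62% | 57% |
| exactly 7 lost per arm | 65% | 59% |
| exactly 8 lost per arm | 62% | 55% |
| 10% chance of zero, normal scores | 65% | 56% |
| 5% chance of zero, uniform scores | 71% | 70% |

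Adding rounding and clipping of scores to 0–18, the results at about 10% loss span roughly 53–68%. For scale, 80% power in the score-zero analysis would need about 110 per group with Mann-Whitney, or about 124 with a t test.

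**The case against.** **The 80% is not an arithmetic slip.** This stands. A reader might infer from the 76% that 64 per group was miscalculated. It was not: it follows from a standard approximation, and the uniform assumption is stated openly. The approximation is optimistic for a shift of this size, by about 4 points, which is small beside the uncertainty in the planning values themselves.

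**57% is the wrong headline.** This also stands. It is the power of a t test that the protocol's own rule would hardly ever choose. The tables in Supplementary Data 5 do show t tests, but they report the per-protocol and sensitivity analyses and do not set the plan for the main one.

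**SD 4 might already include the zeros.** This does not fit. If it did, there would be no reason to raise 64 to 72 for loss.

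**The powered analysis will be reported anyway.** True: the analysis of reached patients is planned as secondary. That softens the consequence, but the power statement still describes an analysis other than the declared main one.

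**Actual loss was lower.** Supplementary Data 5 shows 69 and 68 of 72 with scores, so 7 of 144 (4.9%) were lost. The power statement rests on the planned 10%, and at 5% the main analysis still falls short, at about 71%. A reader might go further and infer that the trial's finding is in doubt. The documents do not support that. Setting 3 and 4 patients to zero in the per-protocol table gives means of 69 × 6.130/72 = 5.88 and 68 × 8.779/72 = 8.29, with t = −3.62 and p = 0.0004. The point concerns the planning statement, not the result.

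**Conclusion.** The concern holds. Sample size and Analysis strategy treat lost patients differently, and the stated 80% is not the power of the declared main analysis. On the protocol's own inputs that power is about 62% with Mann-Whitney at 72 per group, some 18 points lower. The figure depends on equal, random 10% loss in both arms; unequal loss would also bias the comparison. No variant examined at about 10% loss comes near 80%.

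The 76% at 64 per group is a secondary remark about an optimistic approximation.

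A reader might also infer that the main analysis ought to be changed to observed scores. That does not follow. Such a change alters the missing-data assumption and what is being estimated. With 65 reached per group it gives about 81% only with a t test or linear model; the Mann-Whitney figure is about 76–77%. It is a separate choice with its own trade-offs.

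**What to change.** In Sample size, state the power of the analysis declared as main: about 62% at 72 per group with 10% loss scored zero (Mann-Whitney, uniform scores, SD 4, 10 v 12), with loss assumed equal and random in both arms. Add that the figure near 80% belongs to the secondary analysis of reached patients, that it rests on the large-sample efficiency of 1 for uniform data, and that direct simulation of the Mann-Whitney test at 64 per group gives about 76%.

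This rewrites one paragraph and changes neither the design nor the analyses. The cost is a less favourable stated power. Power cannot be recovered once enrolment has ended, so the correction is to the statement only.

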## **Blinding**

Blinding is not applicable to the SIs who have to enroll and randomize patients.

SIs ask patients enrolled in the intervention group not to mention the video clip when they are contacted for the telephone interview. Similarly, investigators conducting the interview never mention the content of the video. These two strategies allow for blinding of the two independent reviewers.

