## Objectives

The aim of this study is to assess the utility of two interventional videos, shown to patients discharged from the ED with a diagnosis of atrial fibrillation or deep vein thrombosis. We have focused our attention on these two medical conditions because they share some important features: they are frequently seen in EDs; their main complication (stroke and pulmonary embolism) can cause significant morbidity and mortality; both conditions and their related complications are probably not

very intuitive to comprehend for the general population. In fact, the understanding of these conditions implies the knowledge of a number of pathological processes, with which most people are unfamiliar.

The primary hypothesis is that patients enrolled in the study group will show a higher degree of comprehension of their medical condition and its related complications, as compared to the control group. Secondly, we will also analyze any possible effect of the videos on the knowledge of the therapy prescribed, return instructions and patients' satisfaction with the quality of communication in the ED.

Eventually, we will examine the association of some factors with the outcomes (age, sex, level of education, atrial fibrillation vs. deep vein thrombosis group).

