### **Control group**

Patients of the control group receive discharge explanations without the aid of any video or graphic support. Following a pragmatic approach, we have asked doctors to express themselves in the way

they are used to in their clinical practice, which is based on the doctor's verbal and non-verbal communication skills.

All patients will receive standard written discharge instructions.

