### **Outcomes**

The main outcome will be patients' comprehension of the domains directly related to the video contents, i.e., knowledge of the *diagnosis* and its potential *complication*, corresponding to interview's questions 1-3-4 (see the attached file *Telephone Interview*).

Secondary outcomes will be the knowledge of the prescribed therapy and patients' satisfaction (see the attached file *Telephone Interview*).

The outcomes will be measured through a telephone interview, consisting of a set of questions specifically designed for the purposes of this study (see the attached file "*Telephone interview*"). The interview is made of six questions, focusing on the different domains of comprehension.

The telephone interview is conducted by one of the two researchers responsible for this task. Audio files are then stored on a computer and subsequently reexamined by both reviewers, who will assign a score to each question contained in the interview (see the attached file "*Telephone interview*").

We developed a scheme to aid the reviewers in the interpretation of patients' answers, to reduce reviewers' inter-operator variability (see the attached file *Interpretation of patients' answers*).

Patients' answers will receive a score on a 4-point Likert scale (ranging from zero to three) from low to high knowledge.

Scores from the two independent reviewers will be summed to obtain an overall score. The score for the main outcomes will therefore range: 0-18 for the main outcome (questions 1-3-4), 0-6 for the knowledge of the prescribed therapy (question 2), 0-12 for patient's satisfaction (questions 5-6).

To the best of our knowledge, no currently available validated questionnaires would serve for the purpose of our study, i.e., for the simultaneous measurement of different domains of comprehension across two different medical conditions.

Hence, we have developed the ad-hoc interview and its related interpretation scheme using face and content validity. Construct validation would require an amount of time and resources equivalent to that of the trial itself, pushing it beyond practical feasibility.

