### **Ethics and dissemination**

The two relevant ethical committees, “*Comitato Etico Pavia*” and “*Comitato Etico di Brescia*”, have approved this protocol, respectively on September 5, 2018 and on May 7, 2019.

All patients or caregivers sign the informed consent prior to study enrolment and randomization.

Once completed the list of SIs, the PIs will communicate their names and affiliations to the Ethical Committees. It may happen during the conduction of telephone interviews, that patients demonstrate a potentially hazardous comprehension deficit of the prescribed therapies, e.g. a patient who ignores or refuses the prescription of parenteral or oral anticoagulants. In such cases, the interviewing PIs will promptly address the patients to his/her GP or send him/her back to the emergency department.

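### Only video patients are asked not to mention the clip; controls get no such request, so the statement that the scoring reviewers are blinded goes further than the safeguard

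*Protocol*

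**What the plan says.** The Blinding section of the protocol names two measures. The first is addressed to one arm: "SIs ask patients enrolled in the intervention group not to mention the video clip when they are contacted for the telephone interview". The second binds the callers: "Similarly, investigators conducting the interview never mention the content of the video". The section then concludes: "These two strategies allow for blinding of the two independent reviewers".

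Four other places bear on this:

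- **Participants timeline:** before discharge, "the SIs will invite patients (or caregivers) to participate to the study, explaining its purpose and the methods used".
- **Ethics and dissemination:** "All patients or caregivers sign the informed consent prior to study enrolment and randomization".
- **Objectives:** "The aim of this study is to assess the utility of two interventional videos".
- **Control group:** "Patients of the control group receive discharge explanations without the aid of any video or graphic support".

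On scoring, the Outcomes section says: "Audio files are then stored on a computer and subsequently reexamined by both reviewers, who will assign a score to each question". Each answer is graded from 0 to 3, the two reviewers' grades are added, and Questions 1, 3 and 4 form the main outcome (0 to 18). The Data management section has reviewers complete the score sheet once they have assessed an interview.

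**The concern.** Reviewer blinding holds only if a recording carries no sign of the arm. The arm can show in two ways: a video patient mentions the clip, or a control says there was none. The protocol guards against the first and leaves the second open. Interviewer silence does not help, because the risk is a spontaneous remark by the participant.

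The main outcome is a graded reading of spoken answers. If a reviewer hears that the speaker had no video and expects less, the grade may drift down. Both reviewers hear the same remark and their grades are summed, so the second reviewer does not offset the first. The drift would favour the intervention. An unqualified claim of blinded assessment would then give the result more protection than the procedure provides.

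**Working it through.** The plan states no figure on this point, so the check is mainly a reading of the passages. Arithmetic serves only to show what order of bias is conceivable.

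**Step 1: who receives the request.** The Blinding section names the intervention group. No matching request to controls appears elsewhere in the protocol, including the description of the control group and the participants' timeline.

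**Step 2: whether controls would know of a video.** Purpose and methods are explained at invitation, and consent precedes randomisation, so the explanation cannot depend on the arm. The aim of the study is to assess two videos. It would be hard to explain purpose and methods without mentioning them. That controls know of the video is therefore very probable but inferred; the protocol does not state it.

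**Step 3: whether a remark reaches the scorers.** Reviewers score the stored audio. The protocol gives no step for screening, muting or logging a revealing remark.

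**Step 4: whether a late remark could matter.** The score sheet is completed once the interview has been assessed. On that reading, a remark made near the end can still colour the grades for Questions 1, 3 and 4.

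**Step 5: how much room the scoring key leaves.**

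- Question 1 asks whether a description is vague, partly logical, incomplete or complete, which leaves clear judgement.
- Question 3 is mainly a count of how many of three criteria are met, with some judgement on each.
- Question 4 is mainly the share of listed symptoms named, which leaves little.

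**Step 6: illustration.** The yardstick from the Sample size section is a median of 10 in controls and 20% more with the video, so 0.20 × 10 = 2 points, with SD 4 and 64 per arm.

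Two inputs are assumptions and are not in the documents: 5% to 20% of control recordings reveal the arm, and each reviewer then marks half a level lower on each affected item.

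Bias = share revealing × 0.5 level × 2 reviewers × number of items affected.

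The effect on type I error uses a normal approximation with a true difference of zero. The standard error is SE = 4 × √(2/64) = 0.707, and the error rate is 1 − Φ(1.96 − bias/SE) + Φ(−1.96 − bias/SE).

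| Items affected | Share | Bias (points) | Bias as % of 2 | Two-sided type I error |
|---|---|---|---|---|
| 1 | 5% | 0.05 × 1 = 0.05 | 2.5% | 5.1% |
| 1 | 20% | 0.20 × 1 = 0.20 | 10% | 5.9% |
| 2 | 20% | 0.20 × 2 = 0.40 | 20% | 8.7% |
| 3 | 20% | 0.20 × 3 = 0.60 | 30% | 13.6% |

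The last row requires a penalty on Question 4 as well, which Step 5 makes unlikely.

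**The case against.** Several counter-arguments have force.

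- **The consent wording is not available.** That controls know of the video is an inference. This stands, and the point is worded accordingly.
- **Nothing in the interview asks about videos.** Question 6, on clarity of communication, might seem a natural prompt, but it offers four fixed options and comes last. It is a weak example, and the point does not rest on it. Its position alone gives no protection, for the reason in Step 4.
- **The written key limits discretion.** This stands for Question 4 and largely for Question 3, and it is why the upper end of the range is generous.
- **A data management plan is cited and may cover revealing recordings.** It may. It is not shown, and a rule there would not make the request in the Blinding section two-sided.

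A reader might infer three stronger things that the documents do not support.

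1. *Reviewers were in fact unblinded.* The documents do not say how often, if ever, controls made such remarks. Video patients might also disclose despite being asked not to.
2. *The reported advantage of the video is an artefact.* Supplementary Data 5 gives a per-protocol difference of 2.65 points. Even the generous 0.6 is well below that, and 0.6 is itself assumed.
3. *The unequal request prepares the arms differently for the questions.* Being asked not to mention a clip reveals no question. The protocol also withholds the interview's exact content from the recruiting doctors and tells them not to anticipate it to patients.

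**Conclusion.** The point holds as a gap in a safeguard. The request is one-sided, controls very probably know of the video, and nothing in the protocol stops or removes a control's remark that none was shown. The unqualified conclusion that the two measures blind the reviewers therefore goes too far.

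The direction, towards the video, assumes that reviewers expect the video to help. The size cannot be derived from the documents: 0.05 to 0.6 points is an illustration resting on the assumed disclosure and penalty rates. If only Question 1 is affected, the same assumptions give 0.05 to 0.20 points. Severity is low to moderate, and the case for change rests mostly on how little it costs.

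**What to change.** Amend the Blinding section in three respects.

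1. Give every participant, patient or caregiver, the same neutral request: not to say on the telephone whether or not a video was shown. Make it ideally before the envelope is opened, so that it cannot differ by arm.
2. Have the interviewer, not a reviewer, mute any such remark in either arm before the file is released for scoring, and log it by arm.
3. Report the number of revealing recordings by arm. An analysis without them should be labelled exploratory, because it selects on behaviour after randomisation that may differ by arm and be related to comprehension.

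For recordings already scored, muting comes too late, but the stored audio still allows a count by arm. The blinding statement should then be qualified.

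The cost is one sentence at recruitment and a little audio editing. One drawback is that the request may draw controls' attention to an aid they did not get, shortly before a satisfaction question; making it before allocation reduces this.
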